### Provisions for post-trial care {30}

Neither the measurements nor the gameplay is expected to result in any significant side-effects, as the game has no graphic depiction of violence and none of our measures are invasive.

### Outcomes {12}

Our primary outcome in this study is the change of iER strategies participants can think of from pre (baseline)- to post-intervention, i.e. if the percentage of participants who improve their knowledge about possible iER strategies is higher in the experimental group compared to the control group. This is done via a vignette-task. The follow-up will be approximately 5 days after baseline measures.

In secondary analyses, we will test iER as a corroborating variable with a questionnaire. The questionnaire was not developed to measure change of iER skills over a short period of time (it asks for iER strategies use in the last 2 weeks) and is thus used as a complementary measure. As the game addresses general topics around emotions additionally to specific iER strategies, we will also examine the change in general emotional competence. Furthermore, effects of sex and gender on strategy choice and feasibility of the game will be examined.

### Participant timeline {13}

This RCT adopts a pre-post-test strategy with the between-participant factor “group” and the within-participant factor “time”. Assessment will include pre-tests (questionnaires; day 1), intervention (playing the game; days 1–5), and post-tests (questionnaires and acceptability measures; days 5–10). After sending the consent forms, every participant will receive the link to the pre-test questionnaires via email. They take approximately  30 minutes to complete. At the end of these questionnaires, participants will be randomly assigned to either experimental or control group and receive the appropriate link for the corresponding game. Additionally, participants are asked to provide a unique identifying code consisting of the first letter of their own first name, the first letter of their mother’s first name, the first letter of their father’s first name, and the day of their birthday. They will use this code in the subsequent parts of the study to allow to link the parts anonymously. The link for the games can be opened as soon as they receive it and accessed with the unique identifying code that they used in the pre-test questionnaires already. Participants are asked to play the game for as long as they want but with the aim to finish it. After that, the participants have 5 days to play the game. They receive the link for post-test questionnaires 5 days after the first link was sent. The post-test questionnaires will take approximately 30 minutes to complete. After 2 days, a generalised reminder is sent to each participant via email to remind them to finish the study if they have not done so already.

The iER AG allows for great variability in playtime, but no matter how long each player takes to finish the game, everyone will have the same amount of iER interactions. As long as they play the game to the end, playtime has no influence on the psychoeducational component but only on the explorative “fun” part of the game. In general, we expect the average playtime to be approximately 3 h in total. The control group will get instructions to play the game as much as they want for the next days. They will receive the final questionnaires 5 days after they started the study. For an overview of the study design, see Fig. 1.

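### The protocol gives three different starting events for the post-test clock, and the one counted from the e-mailed link leaves late starters fewer than the stated 5 days to play

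*Protocol article*

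**What the plan says.** The Participant timeline section {13} sets out the sequence. After consent, "every participant will receive the link to the pre-test questionnaires via email". Randomisation takes place once the pre-test is finished, and only then does the child get the link to the assigned game. "After that, the participants have 5 days to play the game". The nominal schedule, common to both arms, puts the pre-test on day 1, followed by "intervention (playing the game; days 1–5), and post-tests (questionnaires and acceptability measures; days 5–10".

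The time of the post-test is tied to three events:

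- In the general paragraph of {13}: "They receive the link for post-test questionnaires 5 days after the first link was sent".
- In the following paragraph of {13}, about the control group: "They will receive the final questionnaires 5 days after they started the study".
- In Outcomes {12}, for everyone: "The follow-up will be approximately 5 days after baseline measures".

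**The concern.** The three anchors and the 5-day play period agree only if each child completes the pre-test on the day its link is e-mailed. The nominal schedule assumes this, but nothing in the protocol requires it. Access to the game begins at the end of the pre-test, which is also the point of randomisation. A clock that starts with the e-mail therefore runs before the child is in the trial, and any delay comes out of the play period.

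The interval at stake is the one over which the primary outcome is measured. The two arms also depend on it differently. The intervention description {11a} puts completion of the experimental game at about 3 h, and {13} promises equal psychoeducational content only to those who reach the end. The control game has no such end: once won, it can be restarted. A shorter window can therefore remove active content in the experimental arm and has nothing comparable to remove in the control arm.

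**Working it through.** **Which link is the first link.** Section {13} says the pre-test link comes by e-mail. Sequence generation {16a} says the game link is shown inside the questionnaire. At that stage the only link that is sent is the pre-test link, so the general rule most naturally counts from an event before randomisation.

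**Play time before the post-test link.** Let d be the days from the e-mail to completion of the pre-test. The protocol gives no value, so d = 0 to 5 is an assumed range.

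- Clock from the e-mailed link: window = 5 − d.
- Clock from start of study or from baseline: window = 5, taking start and completion of the pre-test as the same day (it takes about 30 minutes).

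| d (assumed) | Clock from e-mail | Clock from start or baseline |
|---|---|---|
| 0 | 5 | 5 |
| 1 | 4 | 5 |
| 2 | 3 | 5 |
| 3 | 2 | 5 |
| 4 | 1 | 5 |
| 5 | 0 | 5 |

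At d = 5 the post-test link arrives at the moment of randomisation. It would precede randomisation only for longer delays.

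**Which clock the team can run.** Confidentiality {27} says e-mail addresses cannot be tied to participants, and {16a} says researchers are blinded. As described, whoever sends the e-mails sees neither when a given child finished the pre-test nor the child's arm. The clock from the e-mailed link is the one they can readily operate. The other two need a trigger that the protocol does not describe.

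**What dilution could cost.** Sample size {14} plans 62 per group for 30% v 10% improving, 80% power, significance level 0.05 (taken as two-sided). Power without continuity correction is

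Φ{[|p1 − p2|√n − 1.96√(2p̄(1 − p̄))] / √[p1(1 − p1) + p2(1 − p2)]}, where p̄ = (p1 + p2)/2.

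With n = 62, p1 = 0.30 and p2 = 0.10: (1.575 − 1.109)/0.548 = 0.851, so power = 0.80. The plan's figure is reproduced.

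Now suppose that a fraction f of experimental participants do not finish because of the short window and improve at the control rate. Then p1 = 0.30 − 0.20f.

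| f (assumed) | p1 | Power at 62 per group |
|---|---|---|
| 0 | 0.30 | 0.80 |
| 10% | 0.28 | 0.73 |
| 20% | 0.26 | 0.64 |

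The protocol gives no value for f. The table shows sensitivity and is not a forecast.

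**Whether the analysis would repair it.** The planned logistic regression includes total playtime and the time from last play to post-test. For the control game no usage data can be collected, and playtime there is a banded self-report. Adjustment would therefore rest on unlike measurements in the two arms.

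**The case against.** A reader might infer that the protocol sets one clock for the experimental arm and another for the control arm, so that with a 2-day delay the intervals are 3 v 5 days, 40% shorter in one arm. The documents do not support this. The sentence about the first link stands in a paragraph on every participant and both games, and no clock specific to the experimental arm is stated anywhere. The 3 v 5 contrast compares two readings of the text, not two arms. The delay arises before randomisation, so under one common clock it is expected to balance. Blinded senders and unlinkable addresses would also make sending by arm hard to operate. All of this stands.

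Four further points limit the concern:

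- The quantity 5 − d is the time to receipt of a link, not the time to outcome. Post-tests run over days 5 to 10, and the protocol does not say that the game closes when the link arrives. A late starter may keep playing, although a reminder follows 2 days after the post-test link and presses towards finishing.
- Even d = 2 leaves 3 days for a game of about 3 h.
- The first link could, less naturally, mean the game link, and then no days are lost.
- The start of the study also precedes randomisation, but only by the length of the pre-test.

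These points weaken the consequence. They do not remove the inconsistency between {12} and {13}, or the shortfall for late starters on the natural reading.

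**Conclusion.** The point holds as an inconsistency in the timing of the primary assessment. Three anchors are given. The general one, read naturally, takes one day from the stated 5-day play period for each day between the e-mail and completion of the pre-test. The main consequence is a shortened window and possible dilution of the effect, not bias between arms. Timing would differ by arm only if the control-group sentence and the general sentence were applied separately.

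The size depends on two quantities that the protocol does not give: the delay d and the share of experimental participants who would fail to finish because of it. No sample-size figure needs to change. The point is worth settling now because the Trial status section describes the trial as not yet recruiting.

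**What to change.** Reconcile {12} and {13} to one anchor for both arms: completion of the pre-test, which is the point of randomisation. Send the post-test link 5 days after it, so that the stated play period holds for any delay. Report days from randomisation to post-test by arm, so that balance can be checked.

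The cost is a few sentences, a survey e-mail setting and one added step. A mailing triggered by pre-test completion needs an address entered at the end of the pre-test. The retention section {18b} describes separate address handling only at the end of the post-test, for the voucher draw, so this is an addition and not something already in place. The address must be kept apart from the answers so that the anonymity statement in {27} remains true.

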**Fig. 1 Fig1:**
[figure not shown]
Study design for an RCT examining the effectiveness of a serious game targeting interpersonal emotion regulation

### Sample size {14}

For the sample size calculation, we consider the percentage of adolescents with a positive change in iER skills between pre- and post-test. We assume that in the experimental group, the number of positive strategies improves by 30%, in the control group it improves by 10%. A chi-square test with a sample size of 62 adolescents per group will have 80% power (significance level 0.05). We expect approximately 30% drop-outs; thus, the total sample size is increased to 180. If in the control group only 1% improves compared to 21% in the experimental group, with this sample size the study has a power of more than 90%.

### Recruitment {15}

Participation is allowed for all people who comply with the inclusion criteria. This study will be conducted online and is consequently not linked to a specific country, but recruitment will take place primarily in German- and English-speaking countries. Given the strict age restriction, a special focus will be put on recruitment from secondary schools. We will actively approach schools in Austria and the UK (this is where the research team is located) and advertise the study via leaflets (paper and email), media presence, and teacher training events. Schools will be likely to participate due to prior and ongoing close collaboration with the research team. Furthermore, the project will be advertised online via social media. Interested participants and/or their parents will receive further information about the study and consent forms via email.

## Assignment of interventions: allocation

### Sequence generation {16a}

After receiving the consent of a parent or legal guardian, the participant will receive a link to the pre-test questionnaires. At the end of the pre-test-questionnaires, participants will be randomised into either experimental or control group. We use SoSci Survey for administering the questionnaires via www.soscisurvey.de [38]. This software allows automated randomisation into different groups. We will use the option to “equally distribute” participants to avoid different group sizes. Depending on the group, participants will then receive the link to either intervention or control game directly in the questionnaire. Participants as well as researchers are blinded during the whole trial.

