### Who will take informed consent? {26a}

Parents/legal guardians of eligible adolescents have to confirm their consent via a pre-scripted email sent to the research group. The lead investigator (GM) will accept the emails. Links to the study questionnaires are only sent after receiving this email. Adolescents will tick a box at the beginning of the pre-test questionnaires asking for their consent.

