## Intervention description {11a}

### Experimental intervention

An iER adventure game was/is currently being designed and developed using both scientific research and co-development workshops with children of the targeted age group to assure that the game has both learning and fun components. It is a single-player role-play/adventure game with 3 levels and a hub world (connecting the levels). It is played from a top-down perspective and created with the commercially available RPG Maker MV. The game is played on a phone or a browser. The game software will allow us to collect data on how the game was played, i.e. which options the participants chose and different time points (e.g. start time, end time). All conversations in the game will be presented in text through conversation windows. Total playtime depends on the player, as the explorative nature of the game allows more or less exploring, but to complete the game, approximately 3 h will be necessary. For the duration of the study, the game will be freely accessible (but will ask for a participant code to enter) via https://dot-game.picapipe.dev/.

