### Plans to promote participant retention and complete follow-up {18b}

Participants are encouraged to finish the study by raffling 5 Amazon vouchers for 50 Euros between all participants who finish the study. Participants have to enter their email addresses at the end of post-test questionnaires. SoSci Survey allows to handle email addresses for this process independent of the rest of the study to ensure anonymity. Furthermore, a standardised email will be sent to every participant 2 days after sending the post-questionnaire link to remind participants to finish the study if they have not done so already.

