### Data management {19}

All measures will be administered via online questionnaires at both pre- and post-test via www.soscisurvey.de [38]. This German server is ISO27001 certified and guarantees organisational, structural, and technical security in accordance with current standards. The server is accessed via SSH-encrypted connection. No data is passed on to third parties. No other person has access to the data, in accordance with section 11 of the Federal Data Protection Act. The server uses SSL encryption. Data is already encrypted on the participant’s browser and only decrypted on the server. No IP addresses are stored in the access log files and no cookies are used.

Due to questionnaires being administered online, missing values can be prohibited by not allowing to skip questions. Outcome data will be checked for unrealistic answer patterns (e.g. always the first option).

Outcome data will be stored on secure, password-protected platforms at the Karl Landsteiner University of Health Sciences. Only direct research associates can access the data.

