### Confidentiality {27}

All data used in this study is anonymized. Email addresses will only be used to send out consent forms and links for the study but cannot be connected to the participants. Each participant will receive a unique identification number at the end of the pre-test questionnaires that they will use to log into the game and in all subsequent study parts. This code will be changed to one number for each participant for analysis as well as any data sharing.

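### The experimental game's login asks only for a code that both arms hold, and the one stated contamination check is a self-report question

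*Protocol article*

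**What the plan says.** **Allocation.** Sequence generation {16a} places randomisation in the survey software: "At the end of the pre-test-questionnaires, participants will be randomised into either experimental or control group". The result is shown at once: "participants will then receive the link to either intervention or control game directly in the questionnaire".

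**Access to the experimental game.** The Experimental intervention section prints the web address and says that for the duration of the study "the game will be freely accessible (but will ask for a participant code to enter"). Participant timeline {13} says which code this is: the games are "accessed with the unique identifying code that they used in the pre-test questionnaires already". There the child composes the code from three first-name initials (own, mother's, father's) and the day of the birthday. Confidentiality {27} describes it differently, as a number that the participant receives at the end of the pre-test.

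**Checks.** Under Plans for assessment and collection of outcomes {18a}, participants are shown a screenshot of the intervention game after the intervention and asked whether they have seen it before. The experimental game also saves the options chosen and the times of play. Neither the primary analysis section nor the section on non-adherence and missing data {20c} gives the screenshot answer, or a comparison of the game log with the allocation, any role.

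**The concern.** The trial compares a psychoeducational game with a puzzle game, so the contrast depends on control children not playing the psychoeducational one. As described, the barrier is a code that every randomised child holds. In the child-made form it is built from facts fixed before allocation and cannot show the arm. The article mentions no check of the code against the arm at login.

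Recruitment focuses on secondary schools, so classmates may be in different arms and an address can be passed on. A control child who plays the experimental game and learns from it raises the control response and dilutes the primary comparison. The screenshot question does not measure this well. A control child who glanced at a classmate's screen and one who finished the game both answer yes, and the answer rests on the child's report.

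**Working it through.** **1. Inputs.** From Sample size {14}: response 30% experimental and 10% control, 62 per group, 80% power, significance level 0.05, 30% drop-out, total 180. Sidedness is not stated; two-sided is used because it reproduces the plan's figure. The share c of analysed controls who play the experimental game is not in the document and is an assumption. Crossovers are assumed to respond at the full 30%.

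**2. The plan's own figure.** Pooled-variance two-proportion formula without continuity correction, with p̄ the mean of p1 and p2:

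n = [1.960·√(2p̄(1−p̄)) + 0.842·√(p1(1−p1)+p2(1−p2))]² / (p1−p2)²

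With p1 = 0.30, p2 = 0.10 and p̄ = 0.20: n = [1.960×0.5657 + 0.842×0.5477]² / 0.04 = 61.6, so 62 per group. This agrees with the plan. For drop-out, 124/0.70 = 177.1, against the stated 180. That inflation covers drop-out only.

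**3. Dilution.** The control rate becomes 0.10×(1−c) + 0.30×c = 0.10 + 0.20c.

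**4. Power at 62 per group.** Power = Φ(z), with z = [(p1−p2)·√62 − 1.960·√(2p̄(1−p̄))] / √(p1(1−p1)+p2(1−p2)).

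| c (assumed) | control rate | z | power |
|---|---|---|---|
| 0% | 0.10 | 0.851 | 80.3% |
| 5% | 0.11 | 0.680 | 75.2% |
| 10% | 0.12 | 0.513 | 69.6% |
| 20% | 0.14 | 0.194 | 57.7% |

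For the 10% row: p̄ = 0.21, and z = [0.18×7.874 − 1.960×0.5760] / 0.5618 = 0.513.

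If all 180 are enrolled and exactly 30% are lost, 63 per group remain and the powers are 80.9%, 75.8%, 70.3% and 58.4%, so the picture does not change.

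**5. What each check can show.** The screenshot question records recognition, by self-report, after the intervention. The game log records play. Entry is by code, so a control child who used their own code would appear in the log and could be matched to the allocation. The log is therefore the better measure, and the trial already collects it. Whether the match works depends on the code. Two children can share three initials and a birth day, so a child-made code may match in error. A number issued by the system could be tied to one record and one arm. The article describes both.

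**The case against.** This is a journal article. The game may check codes against the arm, and the full protocol or analysis plan may say how contamination answers are used. That is fair as to the analysis, and the missing analysis rule would not be a point by itself. What stands is the access route that the article does describe: an open address with a code common to both arms.

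A reader might go further in four ways that the document does not support.

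- **Crossover goes undetected.** The screenshot question exists for this purpose, and the code-based game log offers a second route.
- **Crossover is likely.** Control children are given only their own game's link and participants are described as blinded. The incentive, "raffling 5 Amazon vouchers for 50 Euros between all participants who finish the study", is open to finishers in either arm, so it gives no reason to seek the experimental game. Sharing among classmates is plausible, but no rate can be drawn from the text.
- **A child can reopen the pre-test and be randomised again until the wanted game appears.** A reader might infer this from "No IP addresses are stored in the access log files and no cookies are used" and "Email addresses will only be used to send out consent forms and links for the study but cannot be connected to the participants". But the article does not say whether the link is reusable or single-use. Entry needs a parental consent email first ("Links to the study questionnaires are only sent after receiving this email"), a repeat costs a pre-test of about 30 minutes, and an honest repeat would produce the same child-made code. Repeat randomisation is not established.
- **Allocation concealment is defeated.** Seeing one's own allocation after assignment does not reveal the next one, so the claim under Concealment mechanism {16b} is not contradicted.

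The power figures are also only illustrative, since both the crossover share and the full 30% response are assumed. That stands too.

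**Conclusion.** The point holds for crossover. On the access rule as written, children in both arms can enter the experimental game, and the stated check cannot tell viewing from playing. The statement in section {11c} that automated processes make deviation unlikely is not supported by the access described.

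The size is conditional: about 5, 11 or 23 percentage points of power at assumed crossover shares of 5%, 10% or 20%. The loss is smaller if crossovers respond at less than the experimental rate, and nil if none occur. The direction is towards no difference. The case for acting rests on the low cost of a better control and measure, not on evidence that crossover will be common. Trial status gives the trial as pre-recruitment, so the change can still be made.

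**What to change.** 1. In Experimental intervention and Participant timeline {13}, state that the game accepts only codes allocated to the experimental arm.
2. At minimum, match the codes in the game log to the allocation and report the number of control children found there, beside the screenshot answers. Someone other than the blinded analyst should do the match.
3. Keep the as-randomised comparison as primary, with crossovers counted in the control arm. Add one sensitivity analysis that takes account of crossovers, for example an estimate that uses allocation as the instrument for having played the game, rather than dropping or moving those children.
4. Reconcile Participant timeline {13} (child-made code) with Confidentiality {27} (number received). Steps 1 and 2 both depend on which is used.
5. As a secondary safeguard, state that the first randomisation counts if a child appears twice.

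The cost is a small set-up effort and a list of allowed codes passed from the survey to the game, with no extra participants. One limit remains: a control child who borrows an experimental classmate's code would pass the login and be missed by the match, so the screenshot question is worth keeping.
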